### Testing Procedures

An overview of data procedures completed is shown in Table 1.

**Table 1 table1:** Overview of data collected.

Item		Description
Health and medical questionnaire		Child’s date of birth, gender, birth weight, health conditions, medications, dietary supplements, discretionary salt use habits, parent’s highest level of education attained
Anthropometry		Height, weight, body mass index, waist and hip circumference
Blood pressure		Systolic and diastolic blood pressure
24-hour urine collection		Urinary sodium, potassium, creatinine, total volume
24-hour dietary recall		Food and beverage intake, table salt use
Taste testing		Preference and discrimination with high vs lower salt food item
**Parental component (optional)**		
	Demographics	Date of birth, gender
	24-hour urine collection	Urinary sodium, potassium, creatinine, total volume

### Demographic Characteristics

The parent of each child completed a health information questionnaire (see Multimedia Appendix 1). The questionnaire collected information on the child’s age, gender, birth weight, existing medical conditions, and use of medications or dietary supplements. In Phase 2 of the study, the questionnaire was modified to include an additional question relating to the parent’s highest level of education attained and information on this was retrospectively collected from parents with children participating in Phase 1.

### Discretionary Salt Use

Both parents and children were asked to report on the frequency of discretionary salt use. For parents, three questions were included on the health information questionnaire, two of which applied to the parent’s use of salt, “Q1: Do you add salt during cooking?” (used previously in 2007 CNPAS [66]) and “Q2: Do you place a salt shaker on your table at meal times?”, and one question that related to the child’s own use of salt at meal times, “Q3: Does your child add salt to their meal at the table or sandwich preparation?” For each of these questions, parents could respond “yes usually”, “yes sometimes”, “no”, or “don’t know”. At school on the day of data collection, the study child was also questioned about their own use of table salt. Children were asked, “Does the person who prepares your meal add salt when cooking?” and “Do you add salt to your meal at the table?” (used previously in 2007 CNPAS [66]), to which they could respond “yes, usually”, “yes, sometimes”, “no”, or “Don’t know”.

### Anthropometry

Height, body weight, waist, and hip circumference were measured according to the protocols of the International Society for Advancement of Kinanthropometry [67]. For all measures, children were wearing light clothing with shoes removed. Height was measured to the nearest 0.1 cm using a calibrated portable stadiometer SECA (mod 220) (Hamburg, Germany). Weight was measured to the nearest 0.1 kg using a calibrated FS-127-BRW portable electronic scale (Bradman, MA, USA). A minimum of two measurements were taken for height and weight. If the two measurements were not within 5 mm for height or 0.1 kg for weight, a third measurement was taken. The mean value was used as the final score if two measurements were taken. The median value was used as the final measure if three measurements were taken. BMI was calculated as body weight (kg) divided by the square of body height (m^2^). Age and gender adjusted BMI *z*-scores will be calculated using the LMS method [68] with the 2000 US Centers for Disease Control and Prevention (CDC) Growth Charts acting as the reference population [69]. Participants will be grouped into weight categories (very underweight, underweight, healthy weight, overweight, obese) using the age and gender-specific International Obesity Task Force BMI reference cut-offs for children [70,71].

Waist and hip circumference was measured to the nearest 0.1 cm using a Lufkin Executive Thinline W606PM pocket tape (Sparks, MD, USA). Waist circumference was taken at the end of a normal expiration at the narrowest point between the lower costal border and the top of the iliac crest. Hip circumference was measured at the level of the maximum protrusion of the gluteal muscles. A minimum of two measurements were taken for waist and hip circumference. If the two measurements were not within 10 mm of the first, a third measurement was taken. The mean value was used as the final score if two measurements were taken. The median value was used as the final measure if three measurements were taken.

### Blood Pressure

Blood pressure was measured using an automatic vital signs monitor (OMRON HEM-907) machine according to the US National Heart Lung and Blood Institute Guidelines [72]. Measurements were completed in the sitting position after 10 minutes of rest with the child’s arm positioned at the level of the heart on a rested table. Children were instructed to refrain from talking or coughing during the measurements. To determine the appropriate cuff size, the child’s upper arm (midpoint between the acromion and olecranon) circumference was measured and from this one of three cuff sizes (small 17-22 cm, medium 22-32 cm, large 32-42 cm) was selected for use. The cuff was positioned on the child’s arm by aligning the marked cuff artery indicator with the brachial artery. Once wrapped firmly on the arm, the cuff size was checked by ensuring the marked index line fit within the specified range line on the cuff. If the cuff was noted as being too small or too large, the size up or down was fitted. Three blood pressure readings were taken on the right arm at 1-minute intervals. The average of the last two measurements will be used for analysis.

### Dietary Recall

A three-pass 24-hour dietary recall was used to determine all food and beverages consumed from midnight to midnight on the day prior to the interview. To be consistent with the protocols used in the 2007 CNPAS survey, we utilized the three-pass method. This method includes the following stages: (1) provide a quick list of all foods and beverages, (2) a series of probe questions relevant to each quick list item to gather more detailed information including quantifying the amount consumed, the time and place of consumption, any additions to the food item, brand name, and meal occasion (ie, breakfast, morning tea, lunch, afternoon tea, dinner or supper), and (3) finally, a recall review to validate information and make any necessary adjustments. Portion sizes were estimated using a validated food model booklet and standard household measures. All items were hand-recorded on a food intake form by research staff with a nutrition background and who had received training from an Accredited Practicing Dietitian. It is recognized that children aged 8 years and above have the cognitive ability to recall their own food and beverage intake, whereas in younger children there is a need for a proxy (eg, parent) to help recall intake [73]. In this study, 24-hour recalls were completed on the day of testing at an allocated space within the school. Up to six children were present within each testing session, with children rotating across data collection stations. To avoid young children feeling excluded from certain collection procedures, all children completed the 24-hour dietary recall. However, in analyses related to dietary assessment only recalls in children aged 8 years and above will be utilized. The 24-hour food and beverage intakes will be converted into nutrient intakes, using FoodWorks Version 8, which is linked to the Australian nutrient composition database AUSNUT 2011-13 [74]. Daily sodium (g) intake will be converted to the salt equivalent (g) using the conversion factor 2.543 [18].

The Goldberg cut-off method [75], adjusted for use within the pediatric population [76], will be used to identify participants with implausible energy intakes. Child-specific physical activity levels (PAL) [77] will be used to calculate age and gender-specific Goldberg cut-offs. Schofield equations, specifying age, gender, body weight, and height [78], will be used to calculate each participant’s estimated basal metabolic rate (estBMR). The ratio of each participant’s reported energy intake to estBMR (EI:estBMR) will be compared to the appropriate calculated age and gender-specific Goldberg cut-off value. A participant with an EI:estBMR below the cut-off value will be classified as a low energy reporter.

### Taste Testing Procedures

Tastings were conducted in one-to-one sessions using pre-packed, commercially available high and low salt variants of processed foods that have been identified as major sources of dietary sodium in Australian children (Table 2) [79]. A variety of different core food items such as bread, cereals, and cheese were evaluated. Within core food types tested, the difference in sodium content of the two samples varied between 27% and 84%. For example, one brand of bread with a sodium level of 202mg/100g was compared to another with 511mg/100g (60% difference). There were also differences in the percentage sodium variation within food categories, for example, processed meats varied between 25% and 40%, while for snack foods, potato crisps varied by 94% and tomato sauce by 27%. Differences in sodium content were calculated based on sodium levels provided on package nutrition information panels. To assess taste preference, children were asked to taste high and low salt samples of a food (Figure 2), and asked which they preferred using a forced choice methodology previously shown to be appropriate for use with children [80]. After this, they were asked which of the samples they thought tasted saltier. Participants were then asked to drink some water, and the same process was repeated with a second food type. The two food types tested, with two samples for each, were presented in unmarked wrapping in randomized order. Pairs of low and higher sodium foods were matched as closely as possible for appearance and nutritional composition other than sodium level.

**Table 2 table2:** Foods tested in sensory component.

Bread and cereal	Sandwich fillings	Snack foods
Bread: sourdough white; sourdough wholemeal^b^	Cheese, sliced cheddar^a^	Crisps, potato^a^
Wraps, multigrain^a^	Ham: sliced^a^	Corn chips, plain^a^
Cornflakes^b^	Chicken, sliced roast^a^	Rice crackers, plain^a^
Wheat cereal biscuits^a^		Baked beans^a^
		Tomato sauce^a^

^a^One-paired comparison, using low/high salt food variants.

^b^Two-paired comparisons, using low/high salt and medium/high salt food variants.

**Figure 2 figure2:**
[figure not shown]
SONIC study participant completing data collection procedures.

### 24-Hour Urine Collection

#### Collection Protocol

Participants could commence the 24-hour urine collection either at school or at home over the weekend. Written instructions, tailored for either a school or weekend day collection, were provided for parents, and simplified pictorial instructions were provided for children. All children were instructed to commence the collection by emptying their bladder, discarding this urine, and noting this as the 24-hour collection start time. During the 24 hours following this, all urine voided was collected. Children finished the collection with a final void at the corresponding 24-hour finish time. Urine was collected in 2.5 L wide-mouth, rimmed polypropylene bottles. To assist with urine collection, an additional 500 mL plastic handled jug was provided. Children were asked to report any missed collections or spillages on a urine collection slip, which was returned with the 24-hour urine sample.

School day collections commenced during school hours and at the end of the school day children collected their materials to continue the collection at home. On the following school day, children returned to research staff and finished the collection by providing a final void. Children completing the collection on a weekend day were able to commence the urine collection at any suitable 24-hour period over the weekend, parents recorded start and finish times on the 24-hour urine bottle and a urine collection slip, children were instructed to return completed samples to research staff at school on the following Monday morning.

#### Urinalyses

Urinary sodium and potassium concentration was assessed using indirect ion selective electrodes and urinary creatinine concentration was assessed using the Jaffe reaction [81] on the Siemens Advia 2400 analyzer (Dorevitch Pathology, Melbourne, Vic, National Association of Testing Authorities and Royal College of Pathologists of Australia accredited pathology laboratory). Per participant 2 x 10 mL aliquots were taken for storage and transferred to −80 ^°^C conditions. The molecular weights of sodium (23 g/mol), sodium chloride (58.5 g/mol), and potassium (39.1 g/mol) will be used to convert laboratory of mmol to mg [18].

### Criteria for Assessing Completeness of 24-Hour Urine Samples

If the duration of the collection was not exactly 24 hours (but within 20-28 hours), urinary sodium, potassium, creatinine, and total volume were normalized to a 24-hour period. Following this, urine collections will be considered incomplete and excluded if (1) the timing of the collection was <20 hours or >28 hours, (2) total volume was <300 mL, (3) the participant reported missing more than one collection, or (4) urinary creatinine excretion was less than 0.1 mmol/Kg body weight/day [22,41,82]. A total of 15 participants did not return their urine collection slip, so it was not possible to confirm if they had missed collections or spillages. In these children, the completeness of the 24-hour urine collection was assessed based on the other three criteria. Of the 780 participants, 757 (97.1%) had available results from the 24-hour urine collection (Figure 3). Based on the completeness criteria, 90 participants (11.5%) were classified as providing invalid 24-hour urine samples and will be excluded from analyses. Note the number of invalid urines based on the four criteria (n=125) is greater than the final number of excluded urines (n=90) as some participants’ 24-hour urine collection met more than one of the criteria for invalid urine (Figure 3).

**Figure 3 figure3:**
[figure not shown]
Flow chart of assessment of valid 24-hour urine collections for analysis.

### Sample Size

To estimate mean sodium intake within a 95% confidence interval of +/− 4 mmol/d and assuming a standard deviation of 37 mmol/d (unpublished 24-hour urine pilot data from UK children) [83], a sample size of 329 children was required. We anticipated recruiting 10 children from each school (ie, cluster size n=10) and assumed an intra-cluster correlation (ICC) of .01, giving a design effect (DEFF = 1 - (n-1) ICC) of 1.09. Therefore the sample size after adjusting for clustering was 359 children. Allowing for a 10% loss due to dropout and incomplete urine samples, the target sample size was therefore 395. Given gender differences in sodium intake, we aimed to recruit 395 boys and 395 girls (ie, total n=790).

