The recruitment strategy for children differed between participating government schools, due to constraints placed on the amount of access the project officer could have within the schools. For example, it was not always possible to do the short presentation outlining the study at all schools. Furthermore, study information packs were not distributed to all children at the school. Instead, a “recruitment starter pack”, which contained study information packs, was delivered by the project officer to the school principal, who then organized distribution of the packs to school children. Across all schools, the study was advertised in the school newsletter and parents could then contact the project officer via email or phone expressing their interest in the study and request an information pack. Of the potential 13,045 students enrolled at schools and invited to participate, 582 agreed to participate (response rate=4.5%). To avoid high costs associated with travelling to schools with only a few participants, data collection procedures occurred only at schools with ≥10 participants. In schools (n=11) with <10 participants, children were advised that to participate they would have to travel to Deakin University in Burwood, Melbourne to complete data collection procedures on a Saturday. Of the 41 children that this applied to, 15 agreed to visit Deakin University; however, 7 of these did not attend (ie, dropouts) on the scheduled day of data collection. The remaining 25 were excluded from the study as they were not willing to come to Deakin University. A further 25 children dropped out of the study; reasons for attrition included no longer interested in participating (n=7) or being absent on the day of data collection (n=18). Finally, one child from a school that refused to participate attended the Deakin University data collection day. This child was aware of the study as their mother worked at Deakin University. Written consent was obtained from the child, as well as the child’s parent/caretaker. Due to guidelines for inducements for study participation in government schools, either a book voucher to the value of AU $20 per participant or $100 per school was issued to the school library to thank the children for their participation.

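### Sample size section: the design-effect formula has the wrong sign, the 10% loss is applied as a multiplier (395 instead of 399 per sex), and the 667 valid urines support about ±4.15 mmol/d per sex, not ±4

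*Protocol article*

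**What the plan says.** All of the planning inputs are in the Sample Size section of the protocol article. The precision goal is "To estimate mean sodium intake within a 95% confidence interval of +/− 4 mmol/d", "assuming a standard deviation of 37 mmol/d", from which "a sample size of 329 children was required". With 10 children per school and an ICC of .01, the section continues "giving a design effect (DEFF = 1 - (n-1) ICC) of 1.09", which takes 329 to 359. Then: "Allowing for a 10% loss due to dropout and incomplete urine samples, the target sample size was therefore 395". Citing sex differences in sodium intake, it sets the target at 395 boys and 395 girls, 790 in all.

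The section on completeness of the 24-hour urine samples reports what was obtained. "Of the 780 participants, 757 (97.1%) had available results from the 24-hour urine collection", and on the four completeness criteria "90 participants (11.5%) were classified as providing invalid 24-hour urine samples and will be excluded from analyses". The Results section gives 780 children in 43 schools. The number of valid urines is not printed in the text shown, and neither are the sex split, the observed SD or the observed ICC.

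**The concern.** The ±4 mmol/d half-width is the only quantitative design property given for the primary estimate, and the sentences behind it do not hold together.

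- The design-effect formula cannot produce the value printed beside it. Taken literally, it reduces a clustered sample instead of enlarging it.
- The loss allowance multiplies by 1.10 where it should divide by 0.90, so the target does not quite leave 359 after a 10% loss.
- The article was written after data collection had ended. It prints both the requirement and the attrition, but does not say that the valid collections fall short of the number the precision statement needs.

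At stake is whether a reader may take ±4 mmol/d as the expected precision of the boys' and the girls' means, and whether the calculation can be reused as printed.

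**Working it through.** **Inputs.** From Sample Size: 95% interval, half-width 4, SD 37, 10 per school, ICC .01, loss 10%. From the completeness section: 780, 757 and 90. From Results: 43 schools.

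**1. Reproducing the plan.**
- Unadjusted n = (1.96 × 37/4)² = 328.7, so 329. This matches.
- Design effect 1 + (10 - 1) × .01 = 1.09; 329 × 1.09 = 358.6, so 359. This matches, but only with the plus sign.
- As printed, 1 - (10 - 1) × .01 = 0.91; 329 × 0.91 = 299.4, so 300.
- 359 × 1.10 = 394.9, so 395. This matches.

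**2. Loss allowance done correctly.**
- 359/(1 - 0.10) = 398.9, so 399 per sex, 798 in total.
- 395 × 0.90 = 355.5 remain. Half-width = 1.96 × 37 × √(1.09/355.5) = 4.02.
- The slip is 4 per sex, 8 in total.

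**3. Required against obtained.**
- Required valid urines: 2 × 359 = 718.
- Obtained: 757 - 90 = 667, which is 51 short (51/718 = 7.1%).
- Loss among the 780: 23 without results + 90 invalid = 113; 113/780 = 14.5%, against 10% allowed.
- The 780 are those left after dropout, which the allowance was also meant to cover, so 14.5% does not overstate the loss.

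**4. Expected precision.** Half-width = 1.96 × 37 × √(DEFF/n).

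| Estimate | n | DEFF | Half-width (mmol/d) |
|---|---|---|---|
| Per sex, planned DEFF | 333.5 (even split assumed) | 1.09 | ±4.15 |
| Per sex, 667/43/2 = 7.8 valid per school, ICC .01 | 333.5 | 1.068 | ±4.10 |
| Pooled, planned DEFF | 667 | 1.09 | ±2.93 |
| Pooled, 667/43 = 15.5 valid per school, ICC .01 | 667 | 1.145 | ±3.00 |

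**5. Does the unknown sex split matter?** With 667 in total, one sex must have 333 or fewer. At n = 333 and DEFF 1.09 the half-width is 4.149, so at least one sex exceeds ±4 whatever the split. At 45/55 the two half-widths are 4.37 and 3.95.

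**6. Did the inflation slip cause the shortfall?** Starting from 798 and losing 14.5% leaves 798 × 667/780 = 682, still below 718. At that loss rate about 718/0.855 = 840 would have been needed. The shortfall comes mainly from the realised loss.

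**The case against.** **A 10% allowance is a planning assumption, and exceeding it is not an error.** This stands. The counts are disclosed openly, and the article nowhere claims that ±4 was achieved. Agreement to take part also ran above target: 269 + 582 = 851 against 790. The point about the 667 is therefore that the expected precision should be restated, not that the plan was wrong to assume 10%.

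**The sign is a misprint.** This also stands. The 1.09 appears in the same sentence and the increase from 329 to 359 confirms it, so nothing computed changes.

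**The article never says ±4 per sex, and the primary aim concerns the whole sample.** This stands in part. The per-sex reading is an inference, but a strong one: 395 in total would have served a single overall mean, and sex differences are the only reason given for doubling. On the whole-sample reading the target is met comfortably.

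**The 90 invalid might already include the 23 without results.** On that reading 690 are valid and the loss is 11.5%. That is still above 10% and below 718, at about ±4.08 per sex.

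**Cluster size.** A reader might infer that the design effect is also understated, because "data collection procedures occurred only at schools with ≥10 participants" and the realised mean is 780/43 = 18.1 children per school. The documents do not support this for the per-sex estimate. About 9 participants of one sex per school (7.8 with valid urines) is below the 10 assumed, so 1.09 is slightly conservative there. The larger cluster affects only the pooled mean, which has precision to spare.

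**Conclusion.** The point holds as a minor correction. Two statements in Sample Size are wrong as printed: the sign in the design-effect formula, with no numerical consequence, and the loss inflation, 4 children per sex and ±4.02 instead of ±4 at exactly 10% loss. Separately, 667 valid urines against 718 give an expected half-width of about ±4.1 to ±4.15 mmol/d per sex, and at least one sex is above ±4 for any split. The pooled mean is at about ±3.0.

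These figures rest on the planning SD of 37 and ICC of .01, and on an even sex split where a single per-sex value is quoted. A reader might infer that the study failed to deliver its precision. The documents do not show that: with 667 split evenly and DEFF 1.09, an observed SD of about 35.7 or less would still give ±4, and neither the observed SD nor the ICC is reported. Nor do they support the inference that the inflation slip produced the shortfall.

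**What to change.** In Sample Size:

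- Print the design effect as 1 + (n-1)ICC.
- Add a note that a 10% loss allowance gives 399 per sex (798). Keep 395 and 790 as the target actually used; rewriting a past recruitment target would misreport what was planned.

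There or in the completeness section:

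- State that 667 valid collections were obtained, a 14.5% loss among the 780, against 718 implied by 359 per sex.
- Restate expected precision on the planning assumptions as about ±4.15 mmol/d per sex and ±3.0 pooled, with the even split named as an assumption or replaced by the actual numbers of boys and girls.
- If a range over larger ICCs is shown, label it as an assumption, because the document gives no source for values other than .01. For illustration, with 7.8 valid children per sex per school, the per-sex half-width would be ±4.23 at ICC .02 and ±4.59 at .05.

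The cost is a few sentences. No recruitment, data or planned analysis changes; the stated per-sex precision becomes slightly less favourable.
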